#### Outcomes

The primary outcome of the study is the occurrence of POAF, defined as the occurrence of an irregularly irregular heart rhythm, without detectable P waves, lasting more than 30 s observed during the hospital stay. Patients will be monitored continuously during the entire hospital stay with the Philips Intellivue MP70 patient monitor (Philips, Andover, MA, USA) and alarm strips will be collected for analysis and POAF adjudication. A standard 12-lead electrocardiogram (EKG) will be recorded on a daily basis and collected for analysis and POAF adjudication. Additional 12-lead standard EKGs ordered at the discretion of the caring physician will be collected for analysis and POAF adjudication. An independent committee blinded to group assignment will adjudicate episodes of POAF. The secondary outcome measures of the study will include: (1) time spent in atrial fibrillation, defined as the time from the first evidence of atrial fibrillation to the first evidence of sinus rhythm restoration on cardiac monitoring strips or standard EKG, (2) duration of hospitalization, (3) antiarrhythmic drug use, and (4) need for electrical cardioversion. Safety outcomes will be (1) incidence of left pleural effusion, (2) incidence of pericardial effusion, (3) MAE, and (4) death.

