#### Sample size

Two groups are necessary for this trial: the control group and the intervention group. Based on analysis performed on our aortic surgery database for the years 2012 and 2013, the incidence of POAF in cardiac surgery patients was calculated to be 37.6%. A thorough study of the academic literature, including a meta-analysis of similar studies [10] shows that intervention reduces atrial fibrillation incidence by 50%. Therefore, an atrial fibrillation incidence of 40% in the control group with a proposed decrease of 50% with intervention requires a total of 158 subjects at 80% power and 0.05 alpha. Should the incidence of atrial fibrillation be 30% in the control with a hypothesized 50% decrease, a total of 322 subjects would be required at 90% power. In order to remain conservative, account for 5% protocol violation and 10% loss to follow-up/dropout, and retain power, a total sample size of 350 (175 patients in each treatment group) will be sufficient for this study. Should the incidence of POAF be lower than expected at interim analysis, sample size calculations will be re-estimated to ensure sufficient power at the time of analysis.

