#### Data management

##### Statistical methods

Pre-operative differences between the control and the intervention group will be assessed by univariate analysis. Continuous variables will be analyzed by way of Student’s *t* test or the Mann-Whitney *U* test and categorical variables will be analyzed by use of the chi-squared test. Postoperative differences, including atrial fibrillation and other complications, will also be assessed between the control and intervention groups by way of univariate analysis.

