##### Outcomes

The primary outcome of the study is the occurrence of POAF, defined as the occurrence of an irregularly irregular heart rhythm, without detectable P waves, lasting more than 30 s observed during the hospital stay. Patients will be monitored continuously during the entire hospital stay with the Philips Intellivue MP70 patient monitor (Philips, Andover, MA, USA) and alarm strips will be collected for analysis and POAF adjudication. A standard 12-lead electrocardiogram (EKG) will be recorded on a daily basis and collected for analysis and POAF adjudication. Additional 12-lead standard EKGs ordered at the discretion of the caring physician will be collected for analysis and POAF adjudication. An independent committee blinded to group assignment will adjudicate episodes of POAF. The secondary outcome measures of the study will include: (1) time spent in atrial fibrillation, defined as the time from the first evidence of atrial fibrillation to the first evidence of sinus rhythm restoration on cardiac monitoring strips or standard EKG, (2) duration of hospitalization, (3) antiarrhythmic drug use, (4) need for electrical cardioversion. Safety outcomes will be (1) incidence of left-sided pleural effusion, (2) incidence of pericardial effusion, (3) MAE, and (4) death.

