##### Additional analyses

The primary outcomes will be tested according to the intention-to-treat principle (ITT) where all participants will be included in their assigned treatment groups regardless of the actual procedure performed. Modified intention-to-treat analysis will also be conducted. Per-protocol or as-treated analysis will also be reported as descriptive. The primary outcome analysis will be assessed by logistic regression. Baseline covariates will be included in the regression model for sensitivity analysis. These covariates include: age, sex, diabetes status, ejection fraction, extent of coronary disease, on or off pump procedure, surgical priority, and completeness of revascularization. Secondary outcomes will be analyzed for safety by descriptive statistics.

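### Time spent in atrial fibrillation is defined as a single interval that ends at the first return to sinus rhythm, so read literally it measures first-episode duration and leaves out recurrences

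*Protocol article*

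**What the plan says.** The Background section of the protocol article lists time spent in AF first among the secondary objectives, with no restriction to a first episode or to patients who develop AF.

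The Outcomes section, and the section of the same name under Data management, turn this into a rule: "the time from the first evidence of atrial fibrillation to the first evidence of sinus rhythm restoration on cardiac monitoring strips or standard EKG". Neither section says that later episodes are added, what value a patient without AF receives, or when the clock stops for a patient who leaves hospital in AF.

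On data capture, Outcomes states: "Patients will be monitored continuously during the entire hospital stay". Alarm strips, daily 12-lead EKGs and any additional EKGs are collected, and "An independent committee blinded to group assignment will adjudicate episodes of POAF".

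On analysis there are two statements. Statistical methods says: "Postoperative differences, including atrial fibrillation and other complications, will also be assessed between the control and intervention groups by way of univariate analysis". Additional analyses says: "Secondary outcomes will be analyzed for safety by descriptive statistics".

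**The concern.** The objective concerns how long patients are in AF. The rule starts at the first evidence of AF and stops at the first evidence of sinus rhythm. A patient with a 1-hour first episode and a 30-hour recurrence would score 1 hour out of 31. The measure therefore carries a label that promises AF burden and a definition that delivers something narrower. An effect of pericardiotomy on recurrence would not appear in it at all.

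A second, conditional issue follows from the same wording. A patient without AF has no start time and so no value. If the analysis then used only patients with a value, the groups compared would be selected by an event after randomisation, and that event is the primary outcome the procedure is meant to change. The protection of randomisation would be lost for this outcome.

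**Working it through.** **Reproducing the plan's own figures.** The article gives no figure for time in AF. Its sample sizes for the binary primary outcome supply the AF rates used below, so I checked those first (two-sided alpha 0.05, no continuity correction).

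- 30% vs 15%, 90% power, pooled variance under the null: n per group = [1.960·√(2·0.225·0.775) + 1.282·√(0.30·0.70 + 0.15·0.85)]² / 0.15² = 160.8, rounded up to 161, total 322. This matches.
- 40% vs 20%, 80% power, unpooled variance: n per group = (1.960 + 0.842)²·(0.40·0.60 + 0.20·0.80) / 0.20² = 78.5, rounded up to 79, total 158. This matches ("an atrial fibrillation incidence of 40% in the control group with a proposed decrease of 50% with intervention requires a total of 158 subjects"). The pooled form gives 164.

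Neither figure depends on how time in AF is defined.

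**What the definition counts.** The objective is unrestricted time in AF. The rule has one start (first AF) and one stop (first sinus rhythm). With one episode the two agree. With two or more they differ by the length of every later episode.

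**How many patients have a value under the literal rule.** Inputs: 175 per group, and the rates in Sample size (the historical 37.6% is halved to 18.8%). Patients with a value = 175 × rate; share without = 1 − total/350.

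| Rates | Control | Intervention | Total | Share of 350 without a value |
|---|---|---|---|---|
| 40% / 20% | 70.0 | 35.0 | 105.0 | 70.0% |
| 37.6% / 18.8% | 65.8 | 32.9 | 98.7 | 71.8% |
| 30% / 15% | 52.5 | 26.25 | 78.75 | 77.5% |

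**What recurrence could do (illustration only).** Assumptions not taken from the documents: mean episode 12 h; after each episode a further one follows with probability r, the same in both arms. AF rates are 30% vs 15%. Mean episodes per AF patient = 1/(1 − r), so mean AF time per AF patient = 12/(1 − r) and the share missed by counting only the first episode is r.

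| r | Total AF time per AF patient | Mean over all patients, control (× 0.30) | Mean over all patients, intervention (× 0.15) | AF time missed |
|---|---|---|---|---|
| 0.2 | 15 h | 4.5 h | 2.25 h | 20% |
| 0.4 | 20 h | 6.0 h | 3.0 h | 40% |
| 0.6 | 30 h | 9.0 h | 4.5 h | 60% |

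A simulation under the same assumptions agreed with these values. The first-episode measure behaves as follows:

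- Among AF patients only, it is about 12 h in both arms, so a halved burden does not show.
- Over all patients with zeros for no AF, it is 12 × 0.30 = 3.6 h vs 12 × 0.15 = 1.8 h. The halving shows, but the difference is 1.8 h rather than 3.0 h at r = 0.4.
- If pericardiotomy also halved recurrence (r = 0.4 vs 0.2), total time would be 6.0 h vs 15 × 0.15 = 2.25 h, a ratio of 0.375. The first-episode measure would still give 0.50.

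**The case against.** **The wording may describe each episode.** First evidence could mean the earliest recording of onset and of restoration, applied episode by episode, and the committee adjudicates episodes in the plural. This is possible but is the less literal reading. Even on it, no sentence says that the durations are summed, so the text still does not produce total time in AF.

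**Zeros and discharge in AF can be left to an analysis plan.** This stands. Zero is the ordinary value for someone who had no AF, and an unseen plan may say so and may end the clock at discharge. Neither omission is an error in itself. Counting recurrences is different, because it would depart from the published definition read literally.

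**A reader might infer that the trial will run a t test or Mann-Whitney test on AF patients only.** The documents do not support this. No passage excludes patients without AF. The sentence beginning "Continuous variables will be analyzed by way of" directly follows the one on pre-operative differences, and Additional analyses calls for descriptive statistics for secondary outcomes. The 70% to 78% is therefore what would happen under an unstated choice.

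**A reader might also infer that the result could point against an effective procedure,** if pericardiotomy mainly prevented short episodes. The article says nothing about which episodes it prevents, and the illustration above gives a null result among AF patients, not a reversed one.

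**The recordings may be incomplete.** This also stands. The article says that alarm strips and EKGs are collected, not that full rhythm recordings are kept, so some episode end times may be known only approximately.

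**Conclusion.** The point holds for recurrence. Read literally, the stated rule yields first-episode duration, which is not the objective in the Background section. The size is the share of AF time that falls after the first conversion. The documents give no figure for it; under the assumed recurrence probabilities it is 20% to 60%.

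For patients without AF the point is conditional. The value is undefined, not stated as an exclusion. If the comparison were confined to patients with AF, about 70% to 78% of the 350 would be left out, with twice as many controls as intervention patients remaining, and the comparison would not be a randomised one.

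The effect is limited to one secondary outcome. The primary outcome and the sample size of 350 are untouched, and the interim efficacy rule uses the primary outcome. This should be corrected, but it does not threaten the trial's main conclusion.

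**What to change.** Redefine the outcome, in both places where it appears, as the total duration of all adjudicated AF episodes from end of surgery to discharge. Score zero for patients without AF and end the clock at discharge for those still in AF. Summarise or compare it in all randomised patients by assigned group. Keep first-episode duration among patients with AF as description only. State how an episode end is set when the recordings kept do not show it exactly.

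The cost is a change of wording plus extra strip and EKG review, mainly for patients with recurrent AF, with some end times approximated. One further limit should be accepted openly: with 70% to 78% of values at zero, a rank test would largely repeat the primary outcome, so mean hours per randomised patient by group would be the more informative summary.

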#### Participant timeline

The main outcome of interest is the occurrence of POAF after cardiac surgery. Patients will first be screened for eligibility and willingness to participate in the trial. Then, informed consent will be collected from participating patients, who will be randomized into one of the two study groups. Postoperatively, patients will be closely monitored for the occurrence of atrial fibrillation, pleural and pericardial effusions. Times of event and to discharge will also be assessed. These outcomes will be monitored until the time of the follow-up visit, which will be within 30 days postoperatively for the majority of patients at our institution. Participation until this time point represents complete participation in the trial. We intend to include only patients who have completed follow-up (Fig. 2).

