**Methods/design:**

All patients submitted to cardiac surgery at our institution will be screened for inclusion into the study. The study will consist of two parallel arms with random allocation between groups to either receive a posterior left pericardiotomy or serve as a control. Masking will be done in a single-blinded fashion to the patient. Patients will be continuously monitored postoperatively for the occurrence of atrial fibrillation until discharge. At the follow-up clinic visit (15–30 days after surgery), the primary endpoint (atrial fibrillation) and other secondary endpoints, such as pleural or pericardial effusion, will be assessed. A total sample size of 350 subjects will be recruited.

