##### Analysis population and missing data

Authors do not expect missing data since data collection is during a short period for each patient and only one follow-up visit. In rare instances of missing data, multiple imputation analysis will be utilized. The loss to follow-up will also be reported and compared between the groups using absolute risk differences.

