##### Harms

Serious adverse events (SAE) will be reported to the DMC, the Institutional Review Board and the PI. The study will be interrupted in case of significant differences between groups at interim analyses in terms of SAE during the hospitalization. In cases of mortality, if it is determined that death was a direct result of the trial intervention, the study will be stopped. A subject may be removed from the study if, during the time of surgery, the attending surgeon determines that it would be unsafe to perform the posterior left pericardiotomy due to unexpected difficulty during surgery, additional cardiac surgery, extended cardiac ischemic time, or hemodynamic instability. Removed patients will continue to receive the same care had they not been enrolled. The removed patient will be replaced in the trial should this occur before randomization. The results of the patient will not be included in the dataset or analysis. Since the primary analysis is based on ITT then the patient will be included in the analysis if they are already randomized.

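### The completed-follow-up inclusion sentence contradicts the intention-to-treat primary analysis and, if applied, would select patients on a post-randomisation event

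*Protocol article*

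**What the plan says.** All references are to the protocol article.

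- **Participant timeline.** The section sets the follow-up visit as the end point of participation ("Participation until this time point represents complete participation in the trial") and then states: "We intend to include only patients who have completed follow-up".
- **Additional analyses.** The primary outcome is tested by intention to treat (ITT), under which "all participants will be included in their assigned treatment groups regardless of the actual procedure performed".
- **Harms.** On patients removed during surgery: "Since the primary analysis is based on ITT then the patient will be included in the analysis if they are already randomized".
- **Analysis population and missing data.** "In rare instances of missing data, multiple imputation analysis will be utilized". Loss to follow-up is to be reported and compared between the arms.
- **Outcomes** (given twice, in the same terms). POAF is an episode "lasting more than 30 s observed during the hospital stay", and "Patients will be monitored continuously during the entire hospital stay". Death is the fourth safety outcome.
- **Abstract, Methods/design.** At the clinic visit 15–30 days after surgery, "the primary endpoint (atrial fibrillation) and other secondary endpoints, such as pleural or pericardial effusion, will be assessed". The Participant timeline section likewise has outcomes monitored up to that visit.
- **Sample size.** 350 patients (175 per arm), with allowances of 5% for protocol violation and 10% for loss to follow-up or dropout.

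**The concern.** Whether a patient completes follow-up is not known at consent or at randomisation. A rule that includes only completers can therefore act only after allocation. A randomised patient who misses the visit is left out by the Participant timeline section and kept in by the Additional analyses and Harms sections. The article does not say which prevails.

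The conflict concerns who enters the primary comparison. Return to clinic may depend on the arm, on POAF, on an effusion, on readmission or on death. If that dependence differs between arms, the completers are no longer randomised groups, and the POAF difference can be biased in either direction. The restriction also gains nothing for an outcome that the Outcomes section closes at the end of the hospital stay. Left as it is, the text allows the analysis set to be chosen once the data are known.

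**Working it through.** **1. The statements side by side, for a randomised patient discharged with POAF status recorded who does not attend the visit**

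| Section | Consequence for this patient |
|---|---|
| Participant timeline | left out |
| Additional analyses (ITT) | kept, in the assigned arm |
| Harms | kept, because already randomised |
| Outcomes | POAF status already known |
| Analysis population and missing data | compatible with either |

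The firm conflict is between the first row and the second and third. The imputation sentence does not decide the matter, because completers too can lack a covariate or a single outcome value.

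**2. The plan's own sample sizes**

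Inputs from the Sample size section: 30% v 15% at 90% power, total 322; 40% v 20% at 80% power, total 158; alpha 0.05. Sidedness is not stated, so two-sided is assumed.

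With pooled variance under the null, n per arm = [z₀.₉₇₅ √(2p̄(1−p̄)) + z_power √(p₁(1−p₁)+p₂(1−p₂))]² / (p₁−p₂)².

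- 30% v 15%: p̄ = 0.225, so n = (1.1575 + 0.7445)² / 0.15² = 160.8. This rounds up to 161 per arm, **322 in total**, as stated.
- 40% v 20%: the pooled formula gives 82 per arm (164). The unpooled form gives (1.960 + 0.842)² × (0.24 + 0.16) / 0.20² = 78.5, so 79 per arm, **158 in total**, as stated.

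**3. Power if the completers rule were applied**

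Upper bound on the number dropped: 10% × 350 = 35, leaving 315 (157.5 per arm). Power = Φ{[0.15√n − 1.1575] / √(0.21 + 0.1275)} for 30% v 15%.

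| Analysed | Power, 30% v 15% | Power, 40% v 20% |
|---|---|---|
| 350 (175 per arm) | Φ(1.423) = 92.3% | 98.5% |
| 315 (157.5 per arm) | Φ(1.248) = 89.4% | 97.5% |

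Rounding down to 157 per arm gives 89.3% for 30% v 15%. The standard error rises by √(350/315) = 1.054, about 5%.

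**4. Illustration of selection bias**

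These are assumptions, not figures from the article: no true effect; POAF 30% in both arms; the same fraction m excluded from each arm; control exclusions unrelated to POAF; POAF rate q among the excluded intervention patients. The observed intervention rate is (0.30 − m·q)/(1 − m). For example, with m = 0.10 and q = 0.60 it is (0.30 − 0.06)/0.90 = 26.7%.

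Type I error is Φ(d/SE − 1.96) + Φ(−d/SE − 1.96), where d is the spurious difference and SE its unpooled standard error with 175(1 − m) patients per arm. In the same example, d/SE = 0.0333/0.0507 = 0.657, which gives 10.1%.

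| m | q | Observed intervention rate | Spurious difference (points) | Two-sided type I error |
|---|---|---|---|---|
| 10% | 30% | 30.0% | 0 | 5.0% |
| 10% | 40% | 28.9% | 1.1 | 5.5% |
| 10% | 60% | 26.7% | 3.3 | 10.1% |
| 10% | 100% | 22.2% | 7.8 | 35.1% |
| 5% | 40% | 29.5% | 0.5 | 5.1% |
| 5% | 60% | 28.4% | 1.6 | 6.2% |
| 5% | 100% | 26.3% | 3.7 | 11.6% |

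The first row is the case of no association, where there is no bias. The large errors need exclusion that is strongly related to POAF in one arm only.

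**The case against.** The best defence is that the sentence is a stray remark. It stands in a description of patient flow, names no analysis set, and refers to a figure that is not shown. The sections that do govern the analysis state ITT, and the Harms section says so explicitly for randomised patients. This stands to the extent that the article does not show that patients will be dropped. It shows two rules that cannot both be followed. The wording on the procedure actually performed is aimed mainly at crossover, but the Harms sentence turns on randomisation itself.

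Three stronger readings are tempting and are not supported:

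- **That all deaths before the visit are lost.** A reader might infer this because someone who dies cannot reach the visit and no exception is made. The article never classes deaths as non-completion. It lists death as a safety outcome, and the Harms section sends serious adverse events to the monitoring committee and gives mortality its own stopping rule. Exclusion of deaths is a possible literal reading, no more.
- **That 35 patients with known POAF status would be discarded.** The 10% allowance covers dropout as well as missed visits, and some dropouts may lack the in-hospital outcome. The article also expects missing data to be rare. Thirty-five is an upper bound.
- **That POAF is fully observed at discharge in every patient.** This follows from the Outcomes sections, but the Abstract and the monitoring sentence in Participant timeline extend assessment to the visit.

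It is also fair to say that the power loss is minor: even at the upper bound, power stays at about 89%, against the 90% for which the 322 was calculated.

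**Conclusion.** The concern holds as an internal contradiction. The completed-follow-up sentence is incompatible with the ITT primary analysis in the Additional analyses and Harms sections, and nothing in the article settles which applies. An unseen analysis plan might choose one, but the published text would still state both.

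The consequences are conditional on the sentence being followed. The loss is then at most 35 of 350 patients, about 3 points of power at 30% v 15% (two-sided 0.05 assumed), and a standard error about 5% larger. The more serious risk is selection bias. Its size cannot be derived from the article; under the stated assumptions it runs from none to a type I error of about 35% in the extreme case. Because the defect concerns who enters the primary comparison and costs little to remove, it should be corrected.

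**What to change.** 1. Delete or reword the sentence in Participant timeline. State that the primary analysis includes every randomised patient in the assigned arm, using in-hospital POAF status, whether or not the visit took place. Do not make in-hospital monitoring a condition of inclusion: that too is a post-randomisation event and would conflict with the Harms section.
2. Keep the stated multiple imputation for any missing POAF status and for outcomes measured at the visit.
3. State that all known deaths are counted in all randomised patients.
4. Align the Abstract's Methods/design paragraph and the monitoring sentence in Participant timeline with the in-hospital definition in the Outcomes sections.

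The cost is a few sentences. The in-hospital outcome is already being collected, so the primary analysis needs no new data.
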